### Sample size calculation

The sample size was determined based on 5-year consciousness recovery rates reported in the existing literature on prolonged disorders of consciousness. Chen et al. (13) reported a 5-year consciousness recovery rate of 42.3% in a prospective cohort of Chinese patients; a systematic review by Giacino et al. (14) indicated recovery rates of approximately 35–50% among patients with pDoC following TBI; and a recent longitudinal study by Yan et al. (15) reported a 5-year cumulative recovery rate of 48.7%. Given that the present study enrolls a mixed-etiology cohort (traumatic and non-traumatic) and employs a competing-risk analytical framework, a conservative 5-year cumulative incidence rate of 34% (annual event rate: 8%) was adopted as the basis for sample size estimation, ensuring adequate statistical power. Assuming a hazard ratio (HR) of 1.3, two-sided *α* = 0.05, 80% statistical power, and an exposure proportion of 30%, the required number of events was calculated as 544 using the Schoenfeld formula. Adjusting for an anticipated 15% loss to follow-up over the 5-year period, the target sample size was determined to be 1,000 participants. This sample size will ensure adequate statistical power for the primary survival outcome, support detection of secondary outcomes (functional recovery and quality-of-life changes), enable the identification of moderate effect sizes (Cohen’s *d* ≥ 0.5 or OR ≥ 1.5), and accommodate prespecified subgroup analyses. Prespecified subgroup analyses will evaluate the influence of age, sex, and baseline severity; assuming a subgroup prevalence of 30% and an event rate consistent with the overall cohort, ≥ 80% power will be achievable for detecting HR ≥ 1.5 within each subgroup.

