## Statistical analysis methods

### General principles and descriptive statistics

All statistical analyses will employ two-sided tests with a significance threshold of α = 0.05, and results will be reported with 95% confidence intervals. Bonferroni correction or false discovery rate (FDR) adjustment will be applied to control Type I error inflation in the context of multiple comparisons. Multivariable regression models will be constructed within the competing-risk framework to identify independent prognostic predictors of consciousness recovery, as detailed in the Primary Analysis subsection below. Separately, a dedicated multimodal prognostic prediction model will be developed and validated using a three-stage hierarchically nested approach incorporating LASSO-based variable selection and bootstrap internal validation (1,000 resampling iterations); the C-index will serve as the primary discrimination metric. The full construction procedure for this prediction model is described in the dedicated subsection below.

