### Multimodal prognostic prediction model construction

A multimodal prognostic prediction model will be constructed in three hierarchically nested stages: (1) a Clinical Model incorporating demographic and injury-related variables (age, sex, etiology, GCS at admission, time from injury to enrollment, and baseline CRS-R total score) selected via LASSO regression with 10-fold cross-validation; (2) a Neuroimaging-Augmented Model adding DTI-derived fractional anisotropy (corticospinal tract and corpus callosum) and resting-state fMRI default mode network connectivity to Stage 1; and (3) a Fully Integrated Multimodal Model further incorporating baseline serum biomarkers (NfL, GFAP, S100B). Model discrimination will be quantified by the C-index; incremental value across stages will be assessed using IDI and NRI (95% CIs via bootstrap resampling, 1,000 iterations). The final model will undergo bootstrap internal validation with optimism correction, and calibration will be evaluated using the Harrell calibration plot.

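### Optimism correction is stated for the final model only, so the IDI and NRI used to judge imaging and biomarkers can favour markers that carry no information

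*Protocol article*

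**What the plan says.** The section Multimodal prognostic prediction model construction sets out three nested models.

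- Stage 1 holds clinical variables "selected via LASSO regression with 10-fold cross-validation".
- Stage 2 is described as "adding DTI-derived fractional anisotropy (corticospinal tract and corpus callosum) and resting-state fMRI default mode network connectivity to Stage 1".
- Stage 3 is described as "further incorporating baseline serum biomarkers (NfL, GFAP, S100B".

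On added value the section says that "incremental value across stages will be assessed using IDI and NRI (95% CIs via bootstrap resampling, 1,000 iterations". The next sentence places the correction for overfitting: "The final model will undergo bootstrap internal validation with optimism correction".

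General principles and descriptive statistics adds that "the C-index will serve as the primary discrimination metric". It mentions LASSO and bootstrap internal validation for the three-stage approach as a whole, and sends the reader to the dedicated subsection for the full procedure. Neither place ties the C-index to the comparison between stages.

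**The concern.** Each larger model contains the smaller one and is fitted to the same patients. Extra parameters let it follow chance patterns in those patients, so predicted risks drift apart between recovered and non-recovered patients even when the new markers are noise. Apparent IDI and continuous NRI therefore do not centre on zero when the true gain is zero. A bootstrap interval around an apparent value does not remove this bias. If the models are refitted in each resample, the overfitting occurs again there.

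The multimodal model is the third item under Study objectives, and the Discussion expects the resulting tools to support clinicians and families in individual decisions. A spurious gain would count as evidence for DTI, fMRI and three serum assays as prognostic tests.

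**Working it through.** **Inputs from the protocol article**
- Size: "the target sample size was determined to be 1,000 participants" (Sample size calculation).
- Events: "a conservative 5-year cumulative incidence rate of 34% (annual event rate: 8%) was adopted" (same section). This reproduces: 1 − (1 − 0.08)^5 = 1 − 0.659 = 0.341. It gives 0.34 × 1,000 = 340 recoveries or, after the planned 15% loss, 0.34 × 850 = 289.
- Added markers: 3 in Stage 2 (fractional anisotropy in two tracts, one connectivity index) and 3 in Stage 3, so 6 for Stage 3 against Stage 1.
- The article gives no figure for the incremental-value analysis itself, so there is none to reproduce.

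**Assumptions**
- Binary 5-year outcome, unpenalised logistic models, no censoring or competing death.
- 8 base terms (11 as a check), base AUC about 0.75 (0.67 as a check), normally distributed noise markers.
- Categorical NRI cut-offs of 0.2 and 0.5.

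**Formulas**
- IDI = (mean change in predicted risk among events) − (mean change among non-events).
- Continuous NRI = [P(up | event) − P(down | event)] + [P(down | non-event) − P(up | non-event)].
- Optimism-corrected value = apparent value − mean over resamples of (value of the resample-fitted models in the resample − value of the same models in the original data).

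**Result 1: bias.** At N = 1,000 with 3 noise markers, mean apparent IDI is 0.0028 and mean continuous NRI 0.097; both should be 0. Mean IDI grows with the number of noise markers: 0.0009 for 1, 0.0028 for 3, 0.0054 for 6.

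**Result 2: intervals.** Percentage of 400 null data sets (500 resamples each, N = 1,000, 8 base terms) whose lower 95% limit exceeds 0. The nominal rate is 2.5% and Monte Carlo error is about 2 points.

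| Interval | IDI, 3 markers | Cont. NRI, 3 | Cat. NRI, 3 | IDI, 6 markers | Cont. NRI, 6 | Cat. NRI, 6 |
|---|---|---|---|---|---|---|
| Percentile, refitted | 99.8 | 30.7 | 0 | 100 | 99.3 | 0.5 |
| Percentile, fixed predictions | 19.8 | 26.5 | 6.5 | 59.8 | 52.5 | 13.0 |
| Normal, refitted | 0.3 | 16.8 | 0.5 | 0.7 | 40.3 | 0.7 |
| Basic, refitted | 0 | 17.0 | 3.5 | 0 | 23.5 | 2.0 |
| Percentile, refitted, minus optimism | 2.8 | 7.2 | 0 | 5.0 | 19.3 | 0 |

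The refitted percentile figure for IDI is near 100% because the larger model, refitted to each resample, almost always separates the groups slightly better within that resample, so nearly the whole bootstrap distribution is positive.

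**Result 3: checks**
- N = 850, 3 markers: refitted percentile 100% (IDI) and 32% (continuous NRI); fixed predictions 21% and 26%.
- Base AUC 0.67, 3 markers: refitted 100% and 28%; fixed 22% and 20%.
- One noise marker: refitted 10.5% and 2%.
- Further runs with other settings, 3 markers: refitted 100% for IDI and 36% for continuous NRI; fixed predictions 23-25% and 25-31%.
- A likelihood-ratio test of the added block in the same logistic models rejects in 4.5 to 6.8% with 3 markers, near its nominal 5%.

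**Result 4: LASSO at both stages.** With 10-fold cross-validated LASSO at both stages, 3 noise markers, and the penalty held fixed within 150 resamples, the refitted percentile rate for IDI is 18% or 27%, depending on the penalty rule, and 13% or 26% for continuous NRI. Mean apparent IDI and NRI are then slightly to clearly negative, so the upward shift in the mean is gone but some excess over 2.5% remains.

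**Result 5: effect of correction.** Subtracting optimism brings mean IDI from 0.0028 to 0.0000 with 3 markers. Mean continuous NRI falls only from 0.097 to 0.04, so correction does not fully repair it.

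**The case against.** Four arguments stand against the point.

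- **Uncorrected is an inference.** General principles attaches bootstrap validation and LASSO to the three-stage approach, and nowhere are the stage comparisons called apparent. This is fair as far as it goes. But that section hands the procedure to the dedicated subsection, which has separate sentences for the increment and for the final model and puts the correction in the second only. The narrower reading is the natural one.
- **No decision rule is stated.** The article does not say that a lower limit above 0 counts as improvement, and it also reports the C-index. This stands: the percentages show how the interval behaves under no gain, not how often the authors will make a false claim.
- **Interval type, NRI type, refitting and the reach of LASSO are details that an article may leave to a fuller document.** This stands, and their absence is not the finding. The finding is the pairing that the article does fix: IDI and NRI for the increment, optimism correction for the final model.
- **The likelihood-ratio benchmark comes from plain logistic models.** This also stands. Such a test is not automatically valid after LASSO selection or in a Fine-Gray model, so it is not recommended as such below.

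A reader might infer that the study is almost bound to report a gain from imaging and biomarkers whether or not there is one. The documents do not support that. The near-100% figure belongs to one combination (IDI, percentile interval, refitted and unpenalised added markers), and other choices compatible with the text give rates near 0.

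**Conclusion.** The concern holds in limited form. As written, the added value of Stages 2 and 3 rests on apparent IDI and NRI, and these can favour the larger model when nothing is gained. With unpenalised blocks of 3 markers, N about 1,000, 34% events and base AUC about 0.75, percentile intervals exclude 0 in the favourable direction in roughly 20-25% (fixed predictions) to 100% (refitted) of null data sets for IDI, and in about 26-36% for continuous NRI. Continuous NRI stays inflated, at about 17%, with normal or basic intervals.

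The problem largely disappears for IDI with normal or basic intervals and for categorical NRI with refitting, and it shrinks if LASSO covers every stage. The figures rest on a binary-outcome simplification, and the rates under the actual time-to-event model are not established here. The direction of the bias with unpenalised added markers, and the value of correcting the comparison itself, do not depend on the exact percentages.

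**What to change.** In Multimodal prognostic prediction model construction:

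1. State that bootstrap optimism correction applies to all three stages, repeating the full modelling pipeline, including LASSO, in each resample.
2. Base the claim of incremental value on the difference in optimism-corrected C-index between stages, and report calibration for each stage.
3. Support it with a test of each added marker block that is valid for the model used, for example a robust Wald test in an unpenalised Fine-Gray model with the block prespecified.
4. Report IDI and NRI only as optimism-corrected descriptive values, without a claim of significance.

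No new data are needed. The cost is revised wording and more computing time, and the reported gain from imaging and biomarkers may look smaller.

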## Abstract

**Background:**

Prolonged disorders of consciousness (pDoC), encompassing vegetative state (VS) and minimally conscious state (MCS), represent a formidable clinical challenge characterized by substantial uncertainty in prognostic assessment. Although prior studies have yielded several short-term observational findings, large-scale, long-term longitudinal data delineating the 5-year natural history of pDoC remain scarce—particularly within the Chinese healthcare context. Moreover, existing studies have frequently lacked standardized multimodal assessment protocols and have failed to account for competing risks (e.g., mortality) in statistical models, thereby limiting the accuracy of currently available prognostic tools. The present study aims to address this critical evidence gap through the establishment of a high-quality prospective cohort.

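### The prediction model and its C-index and calibration plot are given no competing-risk form; if deaths are censored by default, predicted recovery is overstated and the calibration check may not show it

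*Protocol article*

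**What the plan says.** Under General principles and descriptive statistics, the protocol article separates two modelling tasks. For the first: "Multivariable regression models will be constructed within the competing-risk framework to identify independent prognostic predictors of consciousness recovery". For the second: "Separately, a dedicated multimodal prognostic prediction model will be developed and validated using a three-stage hierarchically nested approach". For that second model, "the C-index will serve as the primary discrimination metric". The section then sends the reader to the dedicated subsection for the complete construction procedure.

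That subsection, Multimodal prognostic prediction model construction, describes three nested stages. Clinical variables are "selected via LASSO regression with 10-fold cross-validation". Imaging indices and then serum biomarkers are added. On performance it says "Model discrimination will be quantified by the C-index", "incremental value across stages will be assessed using IDI and NRI", and "calibration will be evaluated using the Harrell calibration plot". It gives no model family, no prediction horizon and no handling of patients who die before recovering.

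Elsewhere death is handled explicitly. Primary and secondary outcome variables makes all-cause mortality the competing event for recovery. Primary analysis names the Fine-Gray model both for the main recovery analysis and for the nested comparison of recovered with non-recovered patients. The Background of the abstract says that existing studies "failed to account for competing risks (e.g., mortality) in statistical models, thereby limiting the accuracy of currently available prognostic tools".

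**The concern.** The plan's main methodological claim is that it accounts for competing mortality where earlier prognostic tools did not. The prognostic tool is the one major recovery analysis whose description does not carry that claim through. Each named technique has a standard survival version in which a patient who dies before recovery is treated as censored. In that version:

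- the fitted model estimates the chance of recovery in a hypothetical setting where nobody dies first;
- the observed risk in the calibration plot is 1 minus Kaplan-Meier, which has the same target and the same error;
- in the C-index, a patient who died is not compared with anyone who recovered after that death.

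The Discussion intends the predictions to support individual decisions by clinicians and planning by families. For that use the relevant quantity is the actual probability of recovering within five years, given that death may come first.

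**Working it through.** **Inputs.** From Sample size calculation: 5-year cumulative incidence of recovery 34%, annual event rate 8%, N = 1,000, 15% loss to follow-up. The article gives no mortality figure, so 5-year death before recovery (d) is an assumption, varied from 10% to 40%.

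**Step 1: the plan's own figure.** 1 − (1 − 0.08)^5 = 34.1%. The stated 34% reproduces.

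**Step 2: what a model that censors deaths would estimate.** Take the true cumulative incidence of recovery as F = 0.34 and assume constant cause-specific hazards. Total cumulative hazard: L = −ln(1 − F − d). Recovery's part: R = L × F / (F + d). Estimate with deaths censored: 1 − KM = 1 − exp(−R).

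| d (assumed) | L | R | 1 − KM | Excess over 34% | Ratio |
|---|---|---|---|---|---|
| 10% | 0.580 | 0.448 | 36.1% | 2.1 points | 1.06 |
| 20% | 0.777 | 0.489 | 38.7% | 4.7 points | 1.14 |
| 30% | 1.022 | 0.543 | 41.9% | 7.9 points | 1.23 |
| 40% | 1.347 | 0.619 | 46.1% | 12.1 points | 1.36 |

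Outside this range, d = 5% gives 35.0% and d = 50% gives 52.4%. For scale, the standard error of a 34% proportion with all 1,000 patients followed is √(0.34 × 0.66 / 1,000) = 1.5 points; with 850 followed it is 1.6 points.

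**Step 3: the other reading of the 8% rate.** If 8% a year is the recovery rate among patients still alive and unrecovered, 34.1% is already 1 − KM. With assumed annual death hazards of 0.02, 0.05, 0.10 and 0.15, the true cumulative incidence is 32.6%, 30.4%, 27.3% and 24.6%. The ratios are 1.05, 1.12, 1.25 and 1.39. The conclusion is the same.

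**Step 4: would the calibration plot show it?** This was checked in one simulated cohort: n = 20,000, one standard normal predictor x, annual recovery hazard 0.09·exp(0.7x), annual death hazard 0.10·exp(−0.4x), five years, no loss to follow-up. By five years 32.3% had recovered and 33.5% had died first. A Cox model with deaths censored predicted 39.2% on average. By fifths of the predictor:

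| Fifth | Predicted (deaths censored) | Observed by Kaplan-Meier | Actually recovered |
|---|---|---|---|
| 1 | 16.6% | 16.3% | 10.9% |
| 2 | 27.0% | 27.2% | 20.5% |
| 3 | 36.4% | 37.3% | 29.7% |
| 4 | 47.8% | 47.5% | 39.8% |
| 5 | 68.2% | 68.1% | 60.5% |

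Predicted and Kaplan-Meier values agree within a point in every fifth, so the plot looks good while predictions run 5.7 to 8.0 points too high. In relative terms the error is largest in the lowest fifth, where mortality is highest (16.6 / 10.9 = 1.52). A logistic model counting deaths as non-recovery predicted 32.3% on average, with no overstatement.

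**Step 5: discrimination.** In a random 3,000 of the same cohort the C-index was 0.694 with deaths censored and 0.705 with patients who died kept in the comparison set. The harm lies in absolute risk and calibration much more than in ranking.

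**The case against.** The strongest reply is that the article nowhere says deaths will be censored. The word introducing the prediction model may only separate two purposes, not two frameworks. The Methods part of the abstract says that time-to-event analyses use Fine-Gray models to account for mortality, directly before it describes prediction modelling, and could be read to cover it. LASSO, the C-index, IDI, NRI and a calibration plot also apply to a binary 60-month outcome with deaths counted as non-recovery, and then death causes no overstatement. A C-index and a calibration plot assess predictions and do not create them. Finally, an article condenses a plan, and the variant of each metric is often left to the SAP.

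Much of this stands. A reader might infer that the plan commits to censoring deaths, or that its predictions are overstated. The documents support neither, because the model family is not given. Nor can the metrics cause the error; at most they hide it.

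Three things remain:

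- The General principles section presents the dedicated subsection as the complete procedure and fixes the metrics by name, so this is more than detail left for later. Where Fine-Gray is intended elsewhere, it is written.
- The binary reading appears nowhere. It also sits badly with Loss to follow-up, which right-censors patients at last contact; with 15% loss expected, many would have no 60-month status.
- Even if the model is Fine-Gray, a Kaplan-Meier-based plot would misjudge it: correct predictions would look too low.

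**Conclusion.** The point holds in conditional form. The prediction model is described apart from the competing-risk framework, and neither the model nor its performance measures are given a competing-risk form. That sits against the protocol's own criticism of existing tools and its intended use of the predictions. If the named tools are used in their standard survival form, a true 34% would read as about 36% to 46%, and a Kaplan-Meier-based calibration plot would not reveal it. The effect on the C-index is small.

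The size rests on three assumptions: deaths are in fact censored, 10% to 40% of patients die before recovery, and hazards are constant. At 5% deaths the gap is only one point. This is a gap to close before the model is built, not a demonstrated error in its results.

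**What to change.** In Multimodal prognostic prediction model construction, state that:

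1. all three stages model recovery by 60 months with death before recovery as a competing event, by penalised Fine-Gray or by combined cause-specific models that yield absolute risk;
2. discrimination uses a competing-risk C-index that keeps patients who died in the comparison set as non-recovered;
3. IDI and NRI are computed from the predicted 60-month cumulative incidence;
4. calibration compares that prediction with the Aalen-Johansen cumulative incidence, not with 1 minus Kaplan-Meier.

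Make the sentence on the prediction model in General principles agree. The cost is wording and slightly more analysis work, with no extra data. Compared with a model that censors deaths, reported recovery chances will be less favourable.

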### Secondary analyses and longitudinal data analysis

Secondary outcomes will be analyzed using methods appropriate to each variable type: changes in functional status scores will be modeled using linear mixed-effects models or generalized estimating equations (GEE) to account for within-individual correlations in repeated-measures data; dynamic biomarker changes will be assessed using repeated-measures analysis of variance (ANOVA); quality-of-life scores will be analyzed using generalized linear models; and rehospitalization rates will be modeled using negative binomial regression. All models will account for time effects and between-individual variability.

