**Methods:**

The PDOCC study is a single-center, prospective cohort investigating 5-year disease trajectories in 1,000 patients (aged 18–80) with prolonged disorders of consciousness (VS or MCS ≥ 28 days post-brain injury) (traumatic and non-traumatic etiologies) enrolled at Guangdong Sanjiu Brain Hospital. Data collection includes standardized clinical assessments (CRS-R, GOS-E, DRS, EQ-5D, SF-36), neuroimaging (MRI/DTI/fMRI), and biomarkers (NfL, GFAP, S100B). Follow-up assessments at 3, 6, 12, 24, 36, 48, and 60 months combine in-person evaluations (all timepoints) with remote telephone interviews (3-month intervals after the 6-month visit). Neuroimaging and biomarkers are assessed at baseline and at 6, 12, 24, 36, 48 and 60 months. Primary outcomes are: (1) consciousness recovery, defined as emergence from MCS (eMCS) according to the CRS-R criteria (i.e., consistent functional communication and/or functional object use) sustained for ≥4 consecutive weeks; (2) all-cause mortality; and (3) major cardiovascular events (myocardial infarction, heart failure hospitalization, stroke). Secondary outcomes include: (1) functional status changes (GOS-E, DRS); (2) dynamic biomarker changes (NfL, S100B, GFAP); (3) health-related quality of life (EQ-5D); and (4) rehospitalization rate. Time-to-event analyses will use Fine-Gray competing-risk models to account for mortality as a competing event. Prognostic prediction modeling will be conducted in three sequential stages: a clinical model, a neuroimaging-augmented model (DTI/fMRI), and a fully integrated multimodal model additionally incorporating serum biomarkers (NfL, GFAP, S100B).

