### Variables

#### Primary and secondary outcome variables

The primary outcome variables of this study are as follows: (1) pDoC recovery, defined as emergence from MCS (eMCS), operationalized as achieving a CRS-R communication subscale score ≥2 (functional interactive communication) or a motor subscale score ≥6 (functional object use), confirmed on ≥2 standardized CRS-R assessments conducted ≥7 days apart and sustained for ≥4 consecutive weeks. This criterion applies uniformly to patients with a baseline diagnosis of VS or MCS. All recovery determinations will be adjudicated by the independent Endpoint Adjudication Committee; (2) all-cause mortality, defined as death from any cause at any point during the 5-year follow-up period (up to and including month 60). In the competing-risk analytical framework, all-cause mortality serves as the primary competing risk event for the consciousness recovery outcome. Patients who survive to the end of the 60-month follow-up without having achieved the consciousness recovery endpoint will be administratively right-censored at month 60; and (3) major cardiovascular events (MACE), encompassing myocardial infarction (defined in accordance with the Fourth Universal Definition of Myocardial Infarction, requiring elevated cardiac biomarkers in conjunction with clinical evidence of myocardial ischemia), hospitalization for heart failure (defined as inpatient admission requiring intravenous diuretics or inotropic support), and stroke (confirmed by neuroimaging [CT/MRI] with neurological deficits persisting for more than 24 h).

Secondary outcome variables include: (1) changes in functional status, assessed using the Glasgow Outcome Scale–Extended (GOS-E) and the Disability Rating Scale (DRS) (8, 9); (2) dynamic changes in biomarkers, including serum neurofilament light chain (NfL), glial fibrillary acidic protein (GFAP), S100 calcium-binding protein B (S100B), and other injury- and recovery-related biomarkers; (3) health-related quality of life, evaluated using the EQ-5D questionnaire, with caregiver proxy responses employed when direct patient assessment is not feasible; and (4) rehospitalization rate, documented by recording the frequency and causes of readmission, with particular attention to common complications such as infections, seizures, and respiratory events.

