### Follow-up procedures

Follow-up assessments will employ a hybrid surveillance strategy combining in-person evaluations with remote monitoring. Core neurobehavioral and functional assessments (CRS-R, GOS-E, DRS, EQ-5D, SF-36, FIM, HADS, and Zarit Caregiver Burden Interview) will be conducted at bedside by certified assessors at baseline and at 3, 6, 12, 24, 36, 48, and 60 months (8 assessment timepoints in total, comprising 7 in-person follow-up visits). The Chinese validated CRS-R (7) will be used throughout. Assessors must complete standardized training—covering scoring, ≥10 supervised assessments, and ICC ≥ 0.85 reliability—before independent use. The same assessor will evaluate each participant at all timepoints when feasible; if replaced, inter-rater reliability will be verified against the prior assessor’s last two evaluations. Total and subscale scores will be recorded at each visit. eMCS is defined by subscale-specific behavioral thresholds (per Primary Outcome Variables), not a total score of 23/23, which reflects full neurological recovery rather than functional communication or object use. Neuroimaging investigations (MRI/DTI/fMRI) and serum biomarkers (NfL, S100B, GFAP, and other injury-related biomarkers) will be performed at baseline and at 6, 12, 24, 36, 48 and 60 months. Following the 6-month visit, remote follow-ups will be conducted by telephone interview supplemented by caregiver-reported outcomes at 3-month intervals between scheduled in-person visits, primarily capturing vital status, rehospitalization events, and major adverse events. Remote follow-ups will be administered by uniformly trained research coordinators using standardized scripts, with video calls employed as an adjunct to confirm the patient’s general condition. In-person outpatient visits will be conducted by neurologists and rehabilitation therapists.

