Treatment records (SOC, medications, neuromodulation, including weekly contact time per discipline)	x	x	x	x	x	x	x	x
Neuroimaging (MRI/DTI/fMRI)	x			x	x	x	x	x
Biomarkers (NfL, S100B, GFAP)	x			x	x	x	x	x
Laboratory tests (CBC, electrolytes, etc.)	x							
Primary outcomes (consciousness recovery, all-cause death, major CV events)		x	x	x	x	x	x	x

× Represents data collection timepoint. CRS-R, Coma Recovery Scale-Revised; GOS-E, Extended Glasgow Outcome Scale; DRS, Disability Rating Scale; EQ-5D, EuroQol 5-Dimensions; SOC, Standard of Care; NfL, Neurofilament Light Chain; GFAP, Glial Fibrillary Acidic Protein; CBC, Complete Blood Count.

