### Missing data handling

The distribution and potential mechanisms of missing data will be systematically evaluated, with reporting of the proportion of missingness per variable, the missing data pattern (monotone or non-monotone), and comparisons of baseline characteristics between participants with and without missing data. Primary analyses will assume data missing at random (MAR): complete case analysis will be applied when the proportion of missing data is below 5%; when missingness exceeds 5%, multiple imputation by chained equations (MICE) will be performed using 20 imputation datasets, with imputation models incorporating all relevant variables, and results pooled using Rubin’s rules. Sensitivity analyses will employ pattern mixture models (with *δ*-adjustment parameters) and tipping point analyses to evaluate the robustness of study conclusions under alternative missing data assumptions.

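### The text schedules biomarkers and imaging at month 6 but Table 1 does not, and repeated-measures ANOVA is unsuited to biomarker change in a cohort with deaths and dropout

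*Protocol article*

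**What the plan says.** Biomarker change is a listed secondary outcome: "dynamic changes in biomarkers, including serum neurofilament light chain (NfL), glial fibrillary acidic protein (GFAP), S100 calcium-binding protein B (S100B") and other injury- and recovery-related markers. The section on secondary and longitudinal analyses states that "dynamic biomarker changes will be assessed using repeated-measures analysis of variance (ANOVA"). In the same sentence, "changes in functional status scores will be modeled using linear mixed-effects models or generalized estimating equations (GEE"), with within-patient correlation given as the reason.

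The schedule appears in three places. The abstract says "Neuroimaging and biomarkers are assessed at baseline and at 6, 12, 24, 36, 48 and 60 months". The Follow-up procedures section says that imaging and serum biomarkers "will be performed at baseline and at 6, 12, 24, 36, 48 and 60 months". The Table 1 row headed "Biomarkers (NfL, S100B, GFAP") is marked at baseline, blank at Visit 1 (3 months) and Visit 2 (6 months), and marked at 12, 24, 36, 48 and 60 months. The neuroimaging row has the same pattern.

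On deaths and missing data, "all-cause mortality serves as the primary competing risk event for the consciousness recovery outcome", and mortality is itself a primary outcome. The sample size section anticipates 15% loss over five years. The missing-data section assumes missing at random, uses complete cases below 5% missing, and otherwise says that "when missingness exceeds 5%, multiple imputation by chained equations (MICE) will be performed using 20 imputation datasets".

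**The concern.** Table 1 is the visit-by-visit schedule that site staff are likely to work from. If they follow it, the month-6 imaging and blood samples described in the text will not be taken, and the first measurement after baseline moves to month 12. That affects up to 1,000 scans and 1,000 samples.

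The analysis method raises a separate problem. Classical repeated-measures ANOVA works on complete rows, so one absent sample removes the patient. Over 60 months, in a cohort where death is a primary outcome, the complete rows belong to patients selected on an outcome of the study. The trajectory would then describe fully sampled five-year survivors, although it would be read as the course of the whole cohort. The univariate form also assumes sphericity across intervals that run from months to years.

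**Working it through.** **Schedule, side by side**

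| Source | 0 | 3 | 6 | 12 | 24 | 36 | 48 | 60 | Time points |
|---|---|---|---|---|---|---|---|---|---|
| Abstract, Methods | x | | x | x | x | x | x | x | 7 |
| Follow-up procedures | x | | x | x | x | x | x | x | 7 |
| Table 1, biomarker row | x | | | x | x | x | x | x | 6 |
| Table 1, neuroimaging row | x | | | x | x | x | x | x | 6 |

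Month 6 is the only difference. It is unlikely to come from the PDF conversion: both rows have two empty cells after baseline and then five marks, which fits the eight columns, and the treatment-record row just above carries all eight marks.

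**Who a complete-row ANOVA would analyse**

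The plan states no figure for this analysis, so there is none to reproduce. The calculation below is illustrative.

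Inputs:
- N = 1,000 and 15% loss over five years (sample size section).
- Five-year mortality m: not given in the document; assumed 20, 30 or 50%.
- Share q of due follow-up samples obtained per visit: not given; assumed 100% or 95%.
- k follow-up samples: 6 by the text, 5 by Table 1. The baseline sample is taken as always obtained.

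Formula: complete rows = 1,000 × (1 − m) × 0.85 × q^k, treating death, loss and missed samples as independent.

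Loss alone (m = 0, q = 1): 1,000 × 0.85 = 850.

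With 0.95^6 = 0.735 and 0.95^5 = 0.774:

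| Assumed mortality | No missed samples | q = 95%, 6 samples (text) | q = 95%, 5 samples (Table 1) |
|---|---|---|---|
| 20% | 1,000 × 0.80 × 0.85 = 680 | 680 × 0.735 = 500 | 680 × 0.774 = 526 |
| 30% | 1,000 × 0.70 × 0.85 = 595 | 595 × 0.735 = 437 | 595 × 0.774 = 460 |
| 50% | 1,000 × 0.50 × 0.85 = 425 | 425 × 0.735 = 312 | 425 × 0.774 = 329 |

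**What the missing-data rule does to this**

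The anticipated 15% loss is already above the 5% threshold. There are two readings:
- The rule covers biomarkers. Chained-equation imputation then fills the empty cells. Nothing in the section distinguishes a sample missed by a living patient from a time point after death, so applied as written it would create values after death.
- The rule does not cover biomarkers, because its text speaks of primary analyses. The ANOVA then falls back on complete rows, as in the table above.

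The inverse probability weighting in the section on loss to follow-up is aimed at dropout and does not settle how deaths are treated.

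**The case against.** The two harms are alternatives. If imputation applies, patients are not dropped and the counts above do not arise. If it does not apply, nothing is imputed after death. This stands, and the point is stated conditionally for that reason. A reader might infer that the plan intends to impute biomarkers for dead patients. The document does not say so; it leaves open which route is taken.

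A reader might also infer that most of the collected samples would be wasted. That holds only near the top of the assumed mortality range. Spread deaths and losses evenly over 60 months, so that the share still followed at month t is (1 − m·t/60)(1 − 0.15·t/60), and keep 95% completeness on six follow-up samples. Each enrolled patient then yields on average 5.73, 5.47 or 4.94 samples at 20, 30 or 50% mortality. Of these, 7 × 0.500 = 3.50, 7 × 0.437 = 3.06 or 7 × 0.312 = 2.19 come from complete rows: about 61%, 56% or 44%. A large share is lost, but a majority only at the highest value.

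Two further stronger readings lack support. Nothing in the document shows that the survivors would be those with less injury; selection on survival is enough for the concern. Sphericity can be handled by standard corrections or the multivariate form of the test, so the weakness that remains is the deletion of incomplete rows.

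The consequences are also limited. Biomarker change is one of four secondary outcomes. The prediction model uses baseline biomarkers only, and the recovery and mortality analyses do not depend on the ANOVA. Finally, a mixed model does not by itself resolve death, because under missing at random it implicitly carries trajectories past it. The interpretation therefore has to be stated as well.

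**Conclusion.** Both parts hold. The month-6 conflict is a plain contradiction between the text (seven time points) and Table 1 (six), for biomarkers and for neuroimaging. It rests on no assumption, and its cost is irreversible once the visits have passed.

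Naming repeated-measures ANOVA is a stated choice that does not fit an outcome followed for 60 months with deaths and 15% expected loss. Without imputation it uses at most about 850 of 1,000 patients, and between 680 and 425 under assumed mortality of 20 to 50%, or 500 to 312 if 95% of the six follow-up samples are also obtained per visit. The mortality and completeness values are assumptions. With imputation as written, values after death are not excluded. The choice of route is open, and neither is sound. This should be corrected, but it does not threaten the primary analyses.

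**What to change.** 1. Reconcile Table 1 with the abstract and the Follow-up procedures section for neuroimaging and biomarkers at month 6, before enrolment opens in June 2026.
2. Replace repeated-measures ANOVA by a linear mixed-effects model, which the same section already names for functional scores. Use all samples taken while the patient is alive, with time as a factor and a time by VS/MCS interaction.
3. State that no biomarker value is imputed after death, and that the result is interpreted as the trajectory while alive.

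The cost is slightly more programming, a few changed sentences and one table correction. The sample size does not change.
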